### Sampling and Sample Size

A minimum of 650 participants will be recruited for the study. To ensure an adequate sample size for each of the 13 different device types, a minimum of 50 participants will be recruited for each device group. Owing to the wide variety of devices involved in the study, it was not possible to conduct a power calculation because the device error frequency is known to be disparate among the inhalers involved. On the basis of existing recruitment numbers in published ITE trials [15], alongside the expert clinical opinion from within the protocol development team, a minimum of 50 participants using each device type was felt appropriate to provide a reasonable chance to identify a range of errors.

Potentially, participants may be using several different inhaler device types, so there could be a choice of device type to observe. Throughout the study, the study team will closely monitor the number of participants recruited using each of the 13 device types; therefore, to ensure that the risk of selection bias is distributed equally across all device types, the least commonly recruited device type will be observed in each participant.

Careful consideration has been afforded to ensure that adequate numbers of participants are recruited in all 13 device types included in the study. We will have access to more than 70,000 patients across the Wessex region using participant identification center ITE. Examination of primary care databases will identify those using the inhaler types included in this study, and invitations to participate will be sent to ensure recruitment across all device types.

Recruitment will last for up to 24 months and will not cease at the recruitment of 50 participants in each group, allowing sample sizes greater than this figure.

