### Inhaler Technique Observation and Intervention

Once consent has been obtained, participants will be invited to a suitable clinic room to ensure privacy and a controlled environment with no time pressure. They will be accompanied by a member of the study research team, and the same person will both assess and correct any identified errors in the inhaler technique. The study team members will also record all relevant study data into the CRF. The participants will be asked to demonstrate their inhaler technique using a single-use placebo inhaler device. This is standard clinical practice, and placebo devices, which are identical to the inhaler, are available for all inhaler device types. The technique for using a placebo device is identical to how they would use their inhaler.

The member of the study team will first observe the participant’s inhaler technique using the placebo device for the inhaler that the participant has been prescribed. Any errors in the inhaler technique will be recorded against the device-specific checklist formulated using the manufacturer’s guidelines. This checklist, unique to each inhaler device, includes specific recommended steps to be followed to achieve an optimum inhaler technique, along with any errors in the technique that have been observed.

Participants who are observed to make errors with their inhaler technique will be given feedback by the study team member, and any errors will be highlighted and discussed. The correct technique will be demonstrated by the study team member, with emphasis on correction of the errors, and the participant will then be asked to repeat the demonstration of the inhaler technique to ensure that the errors have been corrected. This method of inhaler technique correction is part of standard clinical practice. A written handout with the correct technique for that device will also be issued to the participant, so that they can refer to this to continue to implement the correct technique.

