If a participant is observed making repeated errors using their device, despite inhaler technique correction, a more suitable inhaler device will be considered. If it is possible to obtain a prescription from a qualified health care professional for an alternative, more suitable device, then this device will be issued during the study visit. The participant will be taught how to use the new device and will be asked to demonstrate the correct technique as per standard clinical practice. Observations with ITE will be recorded in the participants’ CRF for the initial device only. A letter will be sent to the participants’ GP, informing them that a new inhaler device has been issued, with a request to add this to their future repeat prescriptions. If it is not possible to issue an alternative device, a letter will be sent to the participants’ GP recommending a change to a more suitable device, and the participant will require training in the use of this new device. If a participant is participating in another research trial, they will be encouraged to communicate any change in device type or medication with the investigators of the other trial.

If a participant has been prescribed and uses more than 1 inhaler device type, observation and correction of only one device type will be carried out.

To ensure that each member of the study team involved in the inhaler technique observation has the necessary expertise and to ensure standardization across device technique assessment, all members of the study team will attend regular training sessions that will continue every 3 months throughout the study to ensure that competencies have been maintained. Study investigators will have to demonstrate the perfect inhaler technique for each device to be deemed competent. A standard operating procedure for the correct inhaler technique for each device will be produced, and records of competencies will be kept in the study site file.

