#### Primary Analysis

The primary analysis will comprise a comparison of the number of errors made for each inhaler type. As the number of errors is unlikely to be normally distributed, both mean and median values will be presented in all cases. One-way analysis of variance (ANOVA) will be used to determine whether there is a significant difference between the number of errors per inhaler type. If this parametric test is inappropriate based on the distribution of the number of errors, the Kruskal–Wallis (ranked ANOVA) will be used instead.

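### The primary device comparison has no assessor term; if the assessor mix differs between devices, differences in scoring strictness can pass as device differences

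*Protocol article*

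**What the plan says.** The Primary Analysis section compares the number of errors across inhaler types: "One-way analysis of variance (ANOVA) will be used to determine whether there is a significant difference between the number of errors per inhaler type". If the distribution makes this unsuitable, "the Kruskal–Wallis (ranked ANOVA) will be used instead". Distribution is the only stated reason to change test. Means and medians are promised; no interval is stated.

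Under Inhaler Technique Observation and Intervention, scoring is by a single observer: "They will be accompanied by a member of the study research team, and the same person will both assess and correct any identified errors". The same section makes clear that there are several observers, and sets safeguards. The stated aim begins "To ensure that each member of the study team involved in the inhaler technique observation has the necessary expertise" and goes on to standardised assessment. To that end "all members of the study team will attend regular training sessions that will continue every 3 months throughout the study", each device has a standard operating procedure, and competency records are kept. The competence criterion is: "Study investigators will have to demonstrate the perfect inhaler technique for each device to be deemed competent".

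Under Sampling and Sample Size, primary care databases are searched and "invitations to participate will be sent to ensure recruitment across all device types". A participant with several devices is observed on the one least recruited so far. The Recruitment section lists clinics, wards, primary care research clinics, support groups, GP practices, staff and other routes. The Data Analysis overview limits the analysis to 50 randomly chosen participants per device.

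**The concern.** Each checklist step is a yes/no judgement by an observer, so scores given by one person share that person's strictness. One-way ANOVA and Kruskal–Wallis both assume independent observations and have no place for the assessor. If some devices are scored mainly by stricter staff, those devices will appear to produce more errors.

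Several features could make the mix uneven. There are many recruitment settings, some device groups are filled by invitation, and the choice of observed device shifts as recruitment proceeds. Device may therefore track setting and calendar time, and through them the assessor. Random selection of 50 per device does not balance assessors.

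At stake is the study's main product. The section on potential benefits and risks says the study should show which inhalers attract most errors and that this may be passed to manufacturers.

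**Working it through.** **Inputs from the article.** 13 devices, 50 analysed per device, and 13 × 50 = 650, which reproduces the stated minimum. One assessor scores each participant, and there is more than one assessor. No power, standard deviation, assessor number, ICC or allocation is given.

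**Assumptions.** ICC 0.02, 0.05 or 0.10; four or eight assessors (K); normal scores with total variance 1; no true device difference; F-test at 0.05. Each device's assessor shares are drawn from a symmetric Dirichlet distribution with parameter a:
- a = 1 (very uneven): with four assessors, the busiest scores on average 52% of a device's participants.
- a = 3 (moderately uneven): the same figure is 41%.
- a = 1000: even.

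**Simulated rejection rate of one-way ANOVA** (4,000 studies per cell; very uneven / moderately uneven / even):

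| ICC | 4 assessors | 8 assessors |
|---|---|---|
| 0.02 | 11 / 7 / 5% | 9 / 6 / 5% |
| 0.05 | 24 / 10 / 5% | 16 / 8 / 5% |
| 0.10 | 41 / 18 / 5% | 29 / 12 / 5% |

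Repeat runs agree to within about two percentage points. A device-plus-assessor model rejected in 4–6% of studies in every cell.

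**Hand check of one cell** (ICC 0.05, K = 4, a = 1).
- Expected spread of shares: S = (1 − 1/K)/(Ka + 1) = 0.75/5 = 0.15.
- Between-device mean square gains 50 × S × ICC = 50 × 0.15 × 0.05 = 0.375.
- Within-device variance: 1 − ICC × (S + 1/K) = 1 − 0.05 × 0.40 = 0.98.
- Inflation of F: (0.98 + 0.375)/0.98 = 1.38.
- The 5% critical value of F(12, 637) is 1.77, and 1.77/1.38 = 1.28. An F(12, 637) variable exceeds 1.28 with probability about 0.23, which matches the table.
- With even mixes S is about 0, so the level is kept.

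**A different allocation** (3, 5 or 10 assessors; 1,000 studies per cell). With half of each device's participants scored by one assessor, rejection is 0.10–0.15 at ICC 0.02, 0.23–0.31 at 0.05 and 0.43–0.56 at 0.10. It is 0.03–0.05 under balanced and 0.04–0.06 under random allocation. An assessor term gives 0.04–0.06 in all of these. With one assessor per device the rate is 0.38–0.98, and a model term cannot repair it.

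**Intervals, should any be reported.** The design effect for one device under an equal split is 1 + (50/K − 1) × ICC. A proportion of 50% with n = 50 has a half-width of 1.96 × √(0.25/50) = 13.9 points. At ICC 0.05:
- 2 scorers: 1 + 24 × 0.05 = 2.20, giving 13.9 × √2.20 = 20.6 points.
- 4 scorers: 1 + 11.5 × 0.05 = 1.575, giving 17.4 points.
- 8 scorers: 1 + 5.25 × 0.05 = 1.2625, giving 15.6 points.

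**The case against.** The strongest reply is that the condition is not shown. Varied settings describe where participants come from, not who scores them. One team at one hospital does the work, investigators must be competent on every device, and the choice of device for multi-device users follows study-wide counts. All this is consistent with a near-even mix, under which the planned test keeps its level. This stands, so the point is conditional.

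Training, procedures and a fixed checklist should also lower the ICC, and the inflation falls with it. That stands too, but the competence criterion concerns the assessor's own technique, not agreement when scoring patients.

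Type I error is a limited yardstick, since the article expects error frequencies to differ between devices. But assessor strictness can also distort the size and ranking of real differences.

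Finally, this is a condensed article, and the full protocol, analysis plan and case report form are not shown. It cannot be inferred that the assessor goes unrecorded. The device-only primary test, however, is stated.

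A reader might infer that the device comparison is biased, or that the plan's per-device intervals are too narrow. The documents support neither. No uneven allocation is described, and no per-device interval is stated.

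**Conclusion.** The point holds in conditional form. The stated primary test cannot separate assessor from device, and nothing stated keeps the assessor mix even. Under the assumed ICC of 0.02 to 0.10, the false-positive rate is about 7–18% (four assessors) or 6–12% (eight) with moderately uneven mixes. With very uneven mixes it is 11–41% or 9–29%. It is about 5% with even mixes. The true ICC, number of assessors and allocation are unknown. The simulations cover the F-test; Kruskal–Wallis shares the independence assumption but was not simulated. The change is worth making because it is cheap and protects the device ranking.

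**What to change.** - Record an assessor code on each case report form, if it is not already there, and report the assessor-by-device table.
- Fit the device comparison with assessor as a fixed factor, or as a random effect if there are many assessors.
- Where Kruskal–Wallis would apply, use a rank test stratified by assessor, or a count model with an assessor term.
- Take any reported per-device interval from that model. Assessor-robust standard errors are unreliable with few assessors.

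The cost is one form field and a few degrees of freedom (three for four assessors, seven for eight); no extra visits or staff. The limit is that where one person scores a whole device, no term can separate the two. The table would reveal this, and that device's result should then be reported with the caveat.

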#### Secondary Analysis

The secondary analysis will compare the error rates for different background measures. In all cases, the choice of test will depend on whether the number of events is normally distributed. Parametric tests will be used in the first instance, unless there is evidence of nonnormality as assessed using a Shapiro–Wilk test, in which case a nonparametric alternative will be used.

CAT scores will be categorized for the purposes of analysis, with scores of 0-10, 11-20, 21-30, and 31-40 representing mild, moderate, severe, and very severe clinical impact, respectively. One-way ANOVA or Kruskal–Wallis tests will be used to assess whether there is any significant difference in the number of errors among CAT categories.

Exacerbation frequency within the last 12 months will similarly be categorized for the purposes of analysis, with the categories of xx-xx and yy-yy used. One-way ANOVA or Kruskal–Wallis tests will be used to assess whether there is any significant difference in the number of errors between CAT categories.

The association between the number of errors and continuous measures of FEV_1_, FVC, and FEV_1_/FVC ratio will be assessed using bivariate correlation. If the multivariate normality assumptions of the Pearson correlation are not met, logged values of the number of errors will be used to correct for this. If the logged values are still nonnormal, Spearman rank correlation coefficients will be used instead.

The severity of asthma will be measured using the GINA stepwise treatment guide. This measure will be categorized according to the GINA level, and comparisons between the number of errors will be assessed using a one-way ANOVA or Kruskal–Wallis test if the parametric assumptions of the former test are not met.

The severity of COPD will be categorized according to the GOLD stage, which is supplied in the form of categories. One-way ANOVA or Kruskal–Wallis tests will be used to assess whether there is any significant difference in the number of errors among GOLD levels.

Previous device training will be categorized on the basis of whether patients had received previous training. This will be classified as a binary yes or no contrast. Differences in the number of errors will be tested using an unpaired *t* test, or in the event of nonnormality, a Mann–Whitney *U* test.

Among the participants who had received previous inhaler technique training, the cadre of the person giving the training will be categorized as xx, yy, and zz. Differences in the number of errors will be tested using a one-way ANOVA test or a Kruskal–Wallis test if there is evidence of nonnormality.

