#### Primary Objective

The primary objective of this study is to assess the prevalence of device-specific ITE in 13 different devices, using the manufacturers’ guidelines.

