#### Secondary Objectives

The secondary objectives are as follows:

To assess whether the frequency of ITE are associated with participant demographics, respiratory diagnosis, and comorbidities; disease control as measured by questionnaires, such as Asthma Control Questionnaire (ACQ) for asthma and COPD Assessment Tool (CAT) score for COPD, and participant clinical characteristics including exacerbation frequency within the past 12 months; length of time a participant has been using the observed inhaler, along with previous device-specific inhaler technique training (if and when previous training has taken place and given by whom); and levels of behavioral and adherence risk profile as measured by the social, psychographic, usage, and rational (SPUR) profiling tool (Observia).To assess the user error frequency at each step in the device-specific guidelines.To compare user error rates among device types.

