#### Disease Control Questionnaires

Disease control will be assessed using the ACQ for participants with asthma and the CAT for participants with COPD. For participants with a respiratory diagnosis other than asthma or COPD, this will be assessed by recording the number of exacerbations of their respiratory condition in the previous 12 months. An exacerbation is defined as an acute worsening of symptoms requiring treatment with antibiotics or oral corticosteroids. The ACQ [16] is a validated questionnaire for assessing the level of asthma control over the preceding 7 days. The ACQ-6 will be recorded if spirometry is not recorded for the purpose of the study, otherwise the ACQ-7 will be used. The COPD Assessment Test [17] is a validated, 8-item unidimensional measure of health status impairment in COPD. It assists patients and their physicians in quantifying the impact of COPD on the patient’s health. Responses are given on a 5-point scale, with a maximum total score of 40. The higher the score, the greater the impact COPD has on the patient’s health; scores of 0-9 are considered low impact; 10-20, medium; 21-30, high; and >30, very high.

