### Data Analysis

#### Overview

Errors made at each step in each specific device will be tabulated, so that errors and error frequencies can be recorded for each inhaler device against predefined checklists based on the manufacturers’ guidelines. As a minimum of 50 participants are to be recruited for each inhaler device type, there may be a difference in the number of participants in each inhaler group. To reduce bias of over- or underselection, analysis will be restricted to 50 participants using each inhaler device, and participants will be randomly selected for the analysis.

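### The determinant tests take one factor at a time with no term for device, so differences between inhalers can pass for, or hide, effects of training or severity

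*Protocol article*

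**What the plan says.** The Secondary Objectives section sets out "To assess whether the frequency of ITE are associated with participant demographics, respiratory diagnosis, and comorbidities", together with disease control, exacerbations, duration of use, previous training and the SPUR profile. The Secondary Analysis section opens with "The secondary analysis will compare the error rates for different background measures" and then writes out these tests, each with the number of errors as outcome:

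- CAT category, exacerbation frequency, GINA step, GOLD stage and cadre of trainer: one-way ANOVA or Kruskal–Wallis.
- Previous training, yes or no: unpaired *t* test or Mann–Whitney *U*.
- FEV1, FVC and their ratio: bivariate correlation.

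Device enters the Primary Analysis only. The Data Analysis section mentions no covariate, no stratification by device and no scaling of the count to the checklist.

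Elsewhere the article explains the lack of a power calculation by saying that "the device error frequency is known to be disparate among the inhalers involved". The section on technique observation says that every device has a checklist of its own. Under Data Analysis, Overview, "analysis will be restricted to 50 participants using each inhaler device, and participants will be randomly selected for the analysis".

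**The concern.** By the article's own account, device is linked to the outcome. If a determinant is also linked to device, a single-factor test cannot separate the determinant from the inhaler that the person happens to use.

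Two of the named determinants are plausibly linked to device. Previous training is recorded for the device under observation, so its rate can differ from one device to the next. GINA step is a treatment step, so it may go with the inhaler prescribed.

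The bias can run either way: a determinant with no effect can look important, or a real one can be cancelled. The study's stated use is to identify determinants of poor technique, so an error here would carry into advice on training.

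Taking 50 participants per device equalises group sizes. It does not equalise the share trained, or the severity mix, across devices.

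**Working it through.** **The plan's own figure.** "A minimum of 650 participants will be recruited for the study", and "a minimum of 50 participants will be recruited for each device group": 13 × 50 = 650, which reproduces. There is no power formula to check.

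**Inputs.** From the article: 13 devices, 50 analysed per device, and the *t* test or Mann–Whitney *U* for training. Assumed, because the article gives no figures:

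- device mean errors *m* evenly spaced from 1 to 3, as binomial counts out of 10 steps;
- the share trained *p* evenly spaced over the devices, 30–70% or 40–60%;
- no true effect of training, and a two-sided 5% level.

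**Spurious difference.** With no effect inside any device, the expected unadjusted difference, trained minus untrained, is

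Δ = Cov(*p*, *m*) / [p̄(1 − p̄)], with p̄ = 0.5.

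Thirteen evenly spaced points on a 0–1 scale have variance (13² − 1)/(12 × 12²) = 0.0972. If *p* rises in step with *m*:

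- 30–70%: Δ = 0.4 × 2 × 0.0972 / 0.25 = 0.31 errors.
- 40–60%: Δ = 0.2 × 2 × 0.0972 / 0.25 = 0.16 errors.

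**False-positive rate.** The mean of *m* is 2, and the between-device variance is 2² × 0.0972 = 0.39. The mean of *m*² is therefore 4.39. The within-device variance is 2 − 4.39/10 = 1.56, and the total is 1.95. SE = √[1.95 / (650 × 0.25)] = 0.110.

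- 30–70%: z = 0.311/0.1095 = 2.84, so the chance of p < 0.05 is about 81%.
- 40–60%: z = 0.156/0.1095 = 1.42, so about 30%.

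**Simulation of the same set-up**, Mann–Whitney *U* against a linear model with device as a factor:

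| Share trained by device | Unadjusted | Device-adjusted |
|---|---|---|
| Unrelated to device | 5–6% | about 5% |
| 30–70%, paired with devices at random | 12–16% | 4–5% |
| 40–60%, rising with device mean | about 30% | about 5% |
| 30–70%, rising with device mean | about 82% | 5–6% |

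Ranges cover repeated runs.

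**Sensitivity.** With Poisson counts and the *t* test, the two aligned rows become 24% and 74%. If device means span only 1.5–2.5, they become 11% and 28%. With no device differences, the unadjusted rate stays near 5%.

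**Masking.** Add a true reduction of 0.4 errors with training to the aligned 30–70% pattern. The unadjusted difference is 0.31 − 0.40 = −0.09, so z is about −0.8 and the effect is detected in about 13% of trials. The device-adjusted model detects it in about 98%.

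**The case against.** The strongest reply has four parts.

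1. *Nothing shows that determinants vary by device.* This stands as a limit on the claim. A reader might infer that device differences will appear in every determinant test. The article does not support that: it gives no mix of training, severity or diagnosis by device, and without such a link the planned tests keep their 5% level. The 82% needs training rates and error means to rise in the same order across all 13 devices. It is a bad case, not an expected one.

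2. *The tests do not all run on 13 × 50.* Correct. CAT and GOLD apply to COPD, GINA to asthma, and lung function to those with spirometry from routine care or the last 12 months. The figures above are for training only and should not be carried over. Nor is there a written test for diagnosis to criticise.

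3. *An unadjusted association is a legitimate answer to whether errors are associated with a characteristic, and severity may itself influence device choice.* This stands in part. For severity and disease measures, adjusting for device answers a narrower, within-device question, so both estimates have a place. It does not rescue the training comparison, where device is a plain rival explanation.

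4. *The detail may sit in an analysis plan.* This is right for determinants with no written test, such as ACQ, SPUR, duration of use and demographics; their absence from a condensed article is no defect. Nor does the recording of two ACQ versions show a wrong analysis, since no ACQ test is written. The tests at issue here, however, are written out, and they are single-factor.

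**Conclusion.** The concern holds in this form: the named determinant tests ignore a factor that the article itself says is related to the outcome, so device differences *can* appear as determinant effects or mask real ones. Pooling over devices is read from the absence of any by-device analysis of determinants.

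The size is conditional. For training under the assumed values, false positives run from 5% (no link to device) through 12–16% (random pairing) to 30–82% (aligned), with spurious differences of 0.16 to 0.31 errors in the aligned cases. The simulation gives every device 10 steps, so it says nothing about checklist length, and the article does not say that lengths differ.

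This should be fixed before analysis. It does not threaten the study's main result: the objective reads "The primary objective of this study is to assess the prevalence of device-specific ITE in 13 different devices, using the manufacturers’ guidelines", and the primary comparison is by device already. Lung function and disease severity are, moreover, listed as exploratory objectives.

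**What to change.** For each determinant with a written test, add a regression of the number of errors with device as a factor. Model checklist errors out of that device's checklist steps, for example with a binomial model allowing overdispersion. Report write-in additional errors separately, since they have no step to count against. Make the device-adjusted estimate with its 95% CI the main result and keep the planned unadjusted tests as descriptive.

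For CAT, exacerbations, GINA, GOLD and lung function, show both estimates and state that the adjusted one is a within-device association, because disease may have influenced the choice of device.

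Cost: analysis work only, since device and these determinants are already among the recorded data. Device uses up to 12 degrees of freedom. That is little out of 650, but a larger share in the asthma-only, COPD-only and spirometry subsets. There, sparse devices may need grouping, by a rule set before the data are examined.

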#### Exploratory Objectives

The exploratory objectives are as follows:

To categorize ITE as *critical* or *noncritical* and prioritize the importance of these errors by conducting a further study outside the remit of this protocol and involves a Delphi consensus process. Owing to ongoing debate and variations in the definitions of critical and noncritical errors, final definitions will be based on the outcomes of the Delphi consensus process. The information from the Delphi process, along with the data from this prevalence study, will be collated to determine which ITE will be included in a subsequent study, in which a scoring system to quantify ITE will be developed.To correlate severity of disease with ITE if a disease-specific tool is available. The GINA step will be used for asthma and GOLD stage for COPD with spirometry, whereas forced expiratory volume in 1 second (FEV_1_), forced vital capacity (FVC), and FEV_1_/FVC ratio measurements will be used if spirometry is performed as part of standard care.

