#### Participant Clinical Characteristics

This includes patient demographics, such as age and gender, diagnosis requiring inhaler use, and comorbidities.

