#### Spirometry

Spirometry will be conducted using a spirometer conforming to American Thoracic Society/European Respiratory Society standards, as specified by the manufacturer’s instructions. Participants will inhale rapidly and completely from functional residual capacity, then exhale in an initial forced exhalation and continue exhalation until the end of the breath. FEV_1_ (L), FVC (L), and FEV_1_/FVC ratio will be recorded. FEV_1_ and FVC will be documented as both absolute values and as a percentage of the predicted value [18]. A minimum of 3 tests will be performed, with 2 tests within 100 mL or 5% of each other. Spirometry results taken within the last 12 months will be recorded if the current results are unavailable. Spirometry will only be performed and recorded in the CRF if it is required as part of the participant’s routine care standard care (eg, as part of a clinical appointment). For participants recruited outside of the clinical setting, spirometry will not be performed as part of the study assessment.

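### Errors are to be correlated, unadjusted, with FEV1 and FVC on an unnamed scale that reads most naturally as litres, so age, sex and height can be mistaken for disease severity

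*Protocol article*

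**What the plan says.** The protocol article, Secondary Analysis, commits to this: "The association between the number of errors and continuous measures of FEV_1_, FVC, and FEV_1_/FVC ratio will be assessed using bivariate correlation". If normality fails, the error count is logged, and if that fails, Spearman's coefficient is used. No covariate and no unit is named.

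The Spirometry section lists the same three measures with units: "FEV_1_ (L), FVC (L), and FEV_1_/FVC ratio will be recorded". It then adds: "FEV_1_ and FVC will be documented as both absolute values and as a percentage of the predicted value". No percent of predicted is mentioned for the ratio. Spirometry covers only part of the sample: "Spirometry will only be performed and recorded in the CRF if it is required as part of the participant’s routine care standard care". A result from the last 12 months may stand in for a current one.

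The purpose is given under Exploratory Objectives: "To correlate severity of disease with ITE if a disease-specific tool is available". FEV1, FVC and their ratio are named there alongside the GINA step and GOLD stage. The Disease Severity section also relies on lung function, with exacerbations, for participants who have neither asthma nor COPD.

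The Secondary Objectives open with a separate question: "To assess whether the frequency of ITE are associated with participant demographics, respiratory diagnosis, and comorbidities". On what is recorded, Participant Clinical Characteristics says: "This includes patient demographics, such as age and gender, diagnosis requiring inhaler use, and comorbidities". Height is not named there.

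**The concern.** FEV1 and FVC in litres measure body size, sex and age as well as disease. Any adult with an airways condition may enter, so age and stature will vary widely. If older participants make more errors, low FEV1 in litres will go with more errors even when severity plays no part. If age acts in the other direction, a real severity association can be hidden.

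The litre scale thus merges two questions that the study asks separately: whether errors go with demographics, and whether they go with severity. The planned fallbacks deal with the shape of the distribution only. Logging the count or ranking both variables leaves the age, sex and height component in place.

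Leaving the scale open has a second cost. Two versions of FEV1 and FVC will be in the data, and nothing in the article prevents the choice between them from being made after the results are seen.

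**Working it through.** **Plan's own figures.** The article gives no figure for this correlation and no power calculation. The one relevant number is the minimum sample, 13 devices × 50 = 650, which reproduces. Because analysis is restricted to 50 per device, 650 is also the ceiling for any spirometry subset. The actual subset size is not stated, so 150, 325 and 650 are used as assumed values.

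**Induced correlation.** Suppose severity has no effect and errors are linked to FEV1 in litres only through age. Then

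r(errors, FEV1 in L) = r(errors, age) × r(age, FEV1 in L).

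The chance of two-sided p < 0.05 follows from Fisher's z: with z = |atanh(r)| × √(n − 3), it is Φ(z − 1.96) + Φ(−z − 1.96). Both input correlations are assumptions.

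| r(errors, age) | r(age, FEV1 in L) | induced r | n = 150 | n = 325 | n = 650 |
|---|---|---|---|---|---|
| 0.1 | −0.3 | −0.03 | 6.5% | 8.4% | 11.9% |
| 0.2 | −0.5 | −0.10 | 22.9% | 43.7% | 72.3% |
| 0.3 | −0.7 | −0.21 | 73.4% | 96.9% | about 100% |

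Worked line: 0.2 × −0.5 = −0.10; atanh(0.10) = 0.1003; at n = 150, z = 0.1003 × √147 = 1.217; Φ(−0.743) + Φ(−3.18) = 0.229.

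**Simulation as a cross-check.** Assumptions: age mean 62, SD 14; 45% men; mean height 175 cm (men) and 162 cm (women), SD 6.5; a linear prediction equation falling 0.029 (men) or 0.025 (women) L per year of age; percent predicted mean 75, SD 20, independent of age; Poisson errors with mean 2 at age 62, rising with age and not with severity. The average correlations were 0.22 (age, errors) and −0.37 (age, FEV1 in L). Their product is 0.22 × −0.37 = −0.08, and the simulated Spearman correlation of errors with litres was −0.08. Rejection rates for litres were 18%, 31% and 52% at n = 150, 325 and 650. For percent predicted they were 4% to 5%.

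**Distortion of a real association.** A second simulation used age mean 60, SD 15, half men, predicted FEV1 falling 0.027 L per year and rising 4.0 L per metre of height, with the same spread of percent predicted. With a true Spearman correlation of about −0.19 between errors and percent predicted, the litre correlation was about −0.07 when the age-error correlation was −0.19, and about −0.24 when it was +0.19.

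**Limit of the remedy.** Percent predicted holds the nominal rate above only because it was simulated as independent of age. In a sample mixing asthma, COPD and other diagnoses it may track age through diagnosis. If r(age, percent predicted) = −0.3 and r(errors, age) = 0.28, the induced r is −0.3 × 0.28 = −0.084, and at n = 250 the rejection rate is about 26%.

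**The case against.** The strongest objection is that the article never says litres. Both recorded forms are continuous measures of FEV1 and FVC, so the sentence could mean either, and a condensed article may leave the choice to the analysis plan. This stands in part. A reader might infer that the plan has decided against percent predicted; the text does not support that. The litre reading rests on the Spirometry section attaching litres to the same three-item list, and it remains an inference. What the article does fix is an unadjusted bivariate correlation with a set fallback sequence. That stated method is what lets confounding in, so the point is more than a missing detail.

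Second, severity is also tested by GINA step and GOLD stage, so the question does not rest on this correlation alone. That is true for asthma and COPD and limits the impact. For other diagnoses, this correlation is the only planned analysis of lung function.

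Third, the other comparisons in the same section are unadjusted too. That is so, but here the confounder can be part of the measuring scale itself, and a better scale is already recorded.

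Fourth, every magnitude is assumed, and the induced correlations are small: even −0.21 corresponds to 4.4% of variance (0.21² = 0.044). That stands. The rejection rates illustrate the mechanism and are not properties of this study.

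**Conclusion.** The point holds in a limited form. The planned correlation is unadjusted, its scale is unnamed, and on the most natural reading it uses litres. A severity association could then appear or disappear for reasons unrelated to disease.

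On the assumed inputs, the spurious correlation runs from −0.03 to −0.21 and the false-positive rate from near nominal to nearly certain. Where the study falls in that range depends on the age-error correlation and the number with spirometry, neither of which the article gives. If errors prove unrelated to age, sex and height, there is no spurious association.

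A reader might also infer that percent predicted would restore a 5% error rate. That does not follow in a mixed-diagnosis sample, as the last calculation shows; confounding is reduced but may remain.

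The reach is modest: a secondary or exploratory analysis, in the subset with spirometry. No stated figure, the primary analysis or the sample size changes. It is worth correcting because the better measure is already collected.

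**What to change.** In Secondary Analysis, state that FEV1 and FVC enter the correlation as percent of predicted and that values in litres are shown descriptively only. The existing fallback sequence can stay for these two measures.

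For FEV1/FVC, for which no percent of predicted is recorded, specify a partial rank correlation with the number of errors, adjusted for age. Age is already recorded.

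Add a sentence that some confounding by diagnosis may remain, so that the result is read as an association. Settle the wording before the lung-function data are analysed.

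The cost is wording alone: no new data, visits or participants, since percent of predicted is already to be documented wherever FEV1 and FVC are recorded. If percent of predicted was intended all along, the edit only makes that explicit.
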